## Abstract

**Introduction:**

Low back pain (LBP) is the leading contributor to disability globally. It has a substantial impact on the lives of those who experience it, and places considerable economic burden on healthcare systems. Despite these impacts, and the consistency of guideline recommendations, many individuals do not receive recommended LBP management. Structural barriers to accessing timely, evidence-based care, as well as public uncertainty about where to seek appropriate management, can influence the care individuals receive. Telephone and digitally based helplines assist to overcome many traditional barriers to accessing care and offer a scalable platform to improve the delivery of guideline recommended management for LBP. However, uptake of such services can be limited without targeted promotion and patient-centred design. This project aims to codesign, implement and evaluate an upgraded component of an existing Australian helpline service, tailored for people with back pain and supported by a media awareness campaign. This protocol outlines the codesign process, implementation and planned evaluation of the helpline.

**Methods and analyses:**

This protocol uses three complementary frameworks—an iterative codesign process, the Practical Robust Implementation Sustainability Model, and the Reach, Effectiveness, Adoption, Implementation and Maintenance framework—to guide the codesign and development, implementation and evaluation of an upgraded helpline for people with LBP. The codesign process involves key stakeholders, including consumers and clinicians, to inform the development and implementation of both the upgraded helpline service and the media campaign to raise awareness and uptake of the helpline. Data sources will include a pre–post cohort of helpline service users, routinely collected service data (eg, monthly call rate) and health system data to evaluate the broader population level impact (eg, rates of emergency department presentations for LBP in the Australian region targeted by the media campaign). Implementation evaluation will include Reach, Effectiveness, Adoption, Implementation and Maintenance as well as internal and external environmental factors that influence the success of these outcome measures.

**Ethics and dissemination:**

The project was approved by the University of Sydney’s Human Research Ethics Committee (HE001081). This project involves collaboration with consumers, clinicians and other stakeholders to interpret, translate and disseminate research findings to relevant audiences.

STRENGTHS AND LIMITATIONS OF THIS STUDYThis study uses a multiframework approach (iterative codesign, Practical Robust Implementation Sustainability Model and Reach, Effectiveness, Adoption, Implementation and Maintenance) to provide a transparent and theory-informed structure for the design, implementation and evaluation of the upgraded helpline service.Extensive patient and public involvement is embedded throughout the study via the codesign, implementation and evaluation processes with consumers, clinicians and other stakeholders.Multimethods evaluation using quantitative service and cohort data with qualitative insights from stakeholders will provide an improved understanding of potential barriers and facilitators to successful implementation.The use of a pre–post cohort design allows comparison of service effectiveness before and after the upgrade; however, in the absence of a randomised control group, causal inferences are limited.Cohort participants are anticipated to be primarily from the geographical region targeted by the media campaign, which may limit generalisability to other regions with different health service and demographic profiles.

## Introduction

 Despite efforts to change policy^1 2^ and calls to improve practice,^3 4^ low back pain (LBP) remains the leading cause of disability, both in Australia and globally.^5^ LBP has an estimated mean point prevalence of 18%^6^ with a high recurrence rate^7^ and an unfavourable clinical course for those who develop chronic symptoms.^8^ Additionally, LBP is associated with financial hardship and poverty and is the leading chronic condition associated with early workforce retirement.^9 10^ Thus, the economic burden associated with back pain (of which LBP is the largest contributor) in Australia is substantial. Direct health system costs are estimated at $A3.4 billion annually^11^ and indirect costs, associated with loss of productivity and increased welfare payments, exceed $A6 billion.^11^

Guideline management recommendations for LBP have remained relatively consistent for 20 years.^12^ They advocate for a non-pharmacological approach that includes advice and education, self-care and physical activity. Imaging is recommended only for suspected serious pathology and medications should be used judiciously.^13^ However, evidence on contemporary LBP management practices indicates a gap between guideline-recommended care^13^ and the care that patients receive.^14^,^16^ For example, in primary (first-contact) care settings, approximately 25% of patients with LBP are referred for imaging,^16^ more than one-third are prescribed at least one opioid medication within a year of diagnosis,^17^ and only half of Australian patients surveyed recalled receiving education and advice.^18^ In emergency departments (EDs), nearly 70% of patients presenting with LBP receive an opioid medication and almost one-quarter are imaged.^19^ This discrepancy may reflect inequities in access to high-value care and resources, and inadequate support to self-care.

While considerable research has been directed toward improving clinician adherence to LBP guidelines,^20^ addressing structural barriers within the Australian healthcare system may be essential to bridging the gap between guideline-recommended LBP care, and the care that patients receive. Key barriers include inadequate access to timely and appropriate care,^21^ limited public funding to support allied health management^22^ and affordability of ‘out-of-pocket’ costs and private health insurance.^23^ Exacerbating these structural barriers are widespread public misconceptions about the causes of LBP and appropriate management choices. Combined with patients’ lack of awareness about the roles and scope of practice of different healthcare providers, this often results in unsupported self-care, uncertainty about where to seek appropriate care for management of their LBP,^21^ and unnecessary health service utilisation.

The evidence highlights an urgent need to explore alternative strategies to reduce the widespread impact of LBP on individuals and the healthcare system.^2^ Through reformed healthcare pathways and funding models, these strategies should focus on improving access to evidence-based information and care, supporting individuals to remain active at work and in daily life, and reducing unnecessary health service utilisation. One potential solution is the use of helplines—telephone-based services that typically provide free access to health information and advice, with the aim of reducing face-to-face care.^24^ They overcome traditional barriers to accessing care and provide a platform to disseminate evidence-based educational resources at scale and with little geographical limitation. Helplines have been used to empower individuals by providing tailored evidence-based information, emotional support and advice for those with mental health or substance use problems,^25 26^ chronic diseases such as cancer^27^ or rheumatological conditions.^28^ While several helplines exist in Australia to support individuals with musculoskeletal pain or related conditions, such as arthritis, currently no helpline offers a dedicated back pain service that has been evaluated for effectiveness. However, preliminary evidence suggests that LBP interventions delivered by telephone or digitally (eg, mobile apps, websites)^29 30^ can reduce pain intensity and disability when compared with usual care.^31^

Musculoskeletal Health Australia (MHA) is a national peak organisation that represents Australians living with musculoskeletal conditions and aims to support improved musculoskeletal health. MHA established a national helpline (https://muscha.org/helpline) in 2011 to provide free support to people living with musculoskeletal conditions. The helpline is delivered by allied health professionals with clinical experience in managing musculoskeletal pain. It operates from Monday to Friday from 9:00 to 17:00, excluding public holidays (typical business hours in Australia) and is accessible for callers requiring translation services or who have hearing or speaking difficulties. Currently, callers receive one-off, telephone-based support and information. Helpline operators predominantly assist callers with understanding musculoskeletal conditions, managing symptoms including pain, and navigating the complex healthcare system.

Building on this foundation and leveraging digital health technology—including telephone calls, video conferencing and digital health platforms—we will develop and evaluate an upgraded component of MHA’s existing helpline, specifically tailored to individuals experiencing LBP. The enhanced service will incorporate tailored education and advice, empower patients and support self-care, assist patients in navigating the healthcare system and provide follow-up support. The project also includes a media campaign to raise community awareness and encourage greater use of the upgraded helpline.

The aims of the project are:

Upgrade and tailor a component of the MHA helpline service specifically for people with LBP.Implement the upgraded MHA helpline and promote it through a targeted and evaluated mass media campaign.Evaluate outcomes of the service implementation: reach, adoption, effectiveness (including clinical and cost-effectiveness) and maintenance and identify factors contributing to the outcomes.If proven effective, to develop, with our project partners, a plan for an Australia-wide deployment and sustainability of the upgraded MHA helpline.

## Methods

### Study design

This study will use an implementation-effectiveness hybrid design and is funded for the period 1 May 2024 to the 30 April 2029. The study protocol is guided by the Standards for Reporting Implementation Studies.^32^

To guide the design and implementation of the upgraded helpline, an iterative codesign approach, adapted from the Active Implementation Framework,^33^ will be employed.

This will involve iterative phases of engagement with a continuous feedback loop to key stakeholders, including clinicians and consumers and our research partners. This approach aims to ensure the upgraded service remains aligned with stakeholder objectives and the needs of end-users throughout the codesign and implementation process. The planned iterative phases will include:

Exploration—identifying existing issues with the current MHA helpline and establishing the needs of end-users.Design and development—collaborative design of the upgraded helpline and resources needed to successfully implement the service.Testing and refinement—piloting of the upgraded helpline and systems.Implementation—full implementation of the upgraded service and marketing campaign.

The evaluation component will employ a mixed-methods approach to capture implementation process, service outcomes and user experience. Data collection will include: (1) codesign focus group with clinicians and consumers to inform service design and delivery, (2) targeted population surveys to determine helpline awareness before and after the media campaign, (3) pre–post cohort of helpline users to assess participant-reported outcomes, (4) qualitative interviews with a purposive sample of cohort participants and stakeholders to inform implementation and scalability and (5) aggregated data on LBP presentation rates to EDs within the campaign target area. See figure 1 for the project timeline.

**Figure 1 F1:**
[figure not shown]
Project timeline illustrating key phases of data collection, helpline upgrade and media campaign activities, alongside related implementation processes. ED, emergency department; UH, upgraded Helpline.

### Setting and stakeholders

While the research team will assist with the codesign, implementation and evaluation of the upgraded LBP component of the service, the helpline will continue to be managed and operated by MHA. This free service is currently available to all Australians with telephone access. However, for the purposes of the evaluation, the proposed media campaign will be primarily delivered in the Mid North Coast region—a defined Local Health District, within the state of New South Wales (NSW). The Mid North Coast region has a population of 230 000 broadly reflective of national demographics.^34^ The region was chosen due to its concentrated local media which will enable cost-effective dissemination of media campaign messages and maximise the likelihood of helpline awareness and uptake of the service. Therefore, we anticipate most users of the helpline service and recruited cohort participants will be from that geographical area during the campaign period.

The research partners collaborating on this project include:

MHA, primary research partner and helpline operator. MHA also has an associated consumer advisory committee that works closely with the MHA organisation.Agency for Clinical Innovation, a state-based agency working with consumers, clinicians and partnering with the state Ministry of Health and Local Health Districts to improve health systems within NSW, Australia.Australian Self-Care Alliance, a collaborative organisation of healthcare consumers, health promotion charities, policy experts and industry partners that aim to promote self-care among Australians.Northern Sydney Local Health District (NSLHD) Virtual Care and Hospital in the Home services NSLHD, which manages health facilities, including public hospitals, clinics and healthcare services, provided to the geographical region of Northern Sydney, NSW and also delivers a Virtual Care Service model. The NSLHD will provide expertise on remote care delivery.

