### Testing and refinement

The upgraded helpline service and workflows will be tested through a two-step process: (1) A pilot phase with a small number of invited pilot users (non-public release). Pilot users will include members of our research partner organisations, project operations team and MHA’s consumer advisory group, ensuring representation from each partner. We anticipate a minimum of five users. Pilot users will complete the System Usability Scale^40^ to provide structured feedback on the usability of the helpline service. This process will be complemented by an online consultation with pilot users to explore the service functionality, ease of navigation and helpline operator communication. (2) Initial implementation trial and refinement 6 months prior to the media campaign. This will allow time to test the upgraded service in ‘real-world conditions’ prior to the media campaign and an anticipated increase in service users. It is estimated this will involve 50 participants based on MHA’s current monthly rate of LBP callers. These participants will be recruited consecutively following use of the helpline service (see the participant consent and recruitment section) and form the first 50 participants of the postupgrade cohort.

Cohort participants will rate their acceptability of the helpline service across several domains using a modified version of the Theoretical Framework of Acceptability Questionnaire (TFAQ).^41^ In addition, routine service information including the number of calls, call answer rates, peak call times, call duration, number of urgently referred cases, proportion of calls requiring follow-up and average follow-up calls will be collected in the initial implementation period (prior to the media campaign release).

This information will be combined to identify any operational, logistic or technical adaptations that need to be made prior to the full implementation stage.

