### Evaluation

The RE-AIM framework^37^ will be used to evaluate the implementation and effectiveness of the upgraded helpline service. The framework includes five dimensions (RE-AIM) used to understand and evaluate the broader impact of the implementation and intervention across individual, setting and system levels (see table 1). PRISM^36^ will be used as an extension of the RE-AIM framework to guide the exploration of the contextual factors that influence the project outcomes. This includes the characteristics and perspectives of recipients (eg, helpline operators, stakeholders and users), the implementation and sustainability infrastructure (eg, helpline operator capacity vs caller demand), and external environment related to long-term sustainability and scalability of the helpline (eg, government funding and policies for primary care). It can also be used to understand and guide necessary adaptations to improve the intervention implementation process.^49^

**Table 1 T1:** Evaluation of implementation and effectiveness using the RE-AIM framework

Evaluation outcome	Study design	Data source	Time points	Outcome measure	Data analysis	Sample size
Reach						
Reach of the media campaign Reach of the helpline	Cross- sectional Interrupted time series	Population panel surveys Monthly helpline call numbers	(1) Pre–post media campaign (2) 18 months pre to 12 months postmedia campaign	Comparison of helpline awareness between two Local Health Districts LBP monthly call rates	χ² test for proportions Segmented regression	700 panel survey participants (post campaign) All LBP phone calls/services received
Effectiveness						
ED visits for LBP (population level) Self-reported healthcare service utilisation (individual level)	Interrupted time series Independent pre–post cohort design	All LBP ED visits recorded in the Local Health District targeted by the media campaign Pre/Post helpline cohort self-reported data.	18 months pre–post upgrade Baseline, 3 months for each cohort	Monthly LBP ED visits Self-reported healthcare service utilisation	Segmented regression Negative binomial regression for count of healthcare service utilisation	All adult ED LBP visits registered with corresponding health district database 295 cohort participants
Adoption						

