A comparison of primary participant-reported outcome (self-reported healthcare service utilisation) and secondary outcomes, between the preupgraded and postupgraded helpline cohorts will be conducted. The primary outcome will be analysed at 3 months (as part of the effectiveness dimension) and 6 months (as part of the maintenance dimension). Healthcare service use will be collected as count data and analysed using negative binomial regression model. The rate ratio will be estimated comparing the postupgrade cohort to preupgrade cohort. Negative binomial regression will account for individual follow-up time and potential overdispersion due to non-independence of repeated measures. Matching with replacement will be used to address potential imbalances between cohorts in baseline demographics and to account for the anticipated smaller ‘unexposed’ preupgrade cohort compared with the larger ‘exposed’ postupgrade cohort. Sensitivity analyses will be conducted to assess the robustness of the findings.

Individual qualitative interviews will be conducted with purposively selected cohort participants to identify factors and processes that contributed to the helpline uptake, implementation and future scalability. These include acceptability and appropriateness (the extent to which the helpline is perceived as agreeable and relevant); advertising campaign effectiveness; individual factors (eg, participants’ socioeconomic status); and service outcomes (eg, the extent to which the helpline is perceived to be effective, patient centred, timely). Interviews will be semistructured, using a mixture of inductive and deductive thematic analysis drawing on the PRISM framework.^36^ An interview guide will be used to ensure the same topics are explored across individual interviews.

Focus groups with key stakeholder groups will be conducted online to identify factors and processes that contributed to helpline uptake, implementation and future scalability. The interview guide will be informed by findings from the implementation phase to align with observed barriers and enablers. Focus group data will be analysed using a combination of inductive and deductive approaches, drawing on the PRISM framework to guide interpretation.

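### The only balancing step named for the primary pre-post rate ratio is matching on baseline demographics, although region and recruitment route change along with the upgrade, so a shift in case mix could pass for an upgrade effect.

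*Protocol article*

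**What the plan says.** The Effectiveness and Data analysis sections define the primary participant-level comparison as a negative binomial rate ratio of self-reported healthcare use at 3 months between two independent cohorts, one using the original service and one the upgraded service.

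- **Source of the pre-upgrade cohort.** Setting and stakeholders: "This free service is currently available to all Australians with telephone access". About 50 participants are anticipated before the upgrade.
- **Source of the post-upgrade cohort.** Testing and refinement: an estimated 50 users are recruited in the six months before the campaign and "form the first 50 participants of the postupgrade cohort". The enrolment target is 245. For the campaign period, Setting and stakeholders states that "we anticipate most users of the helpline service and recruited cohort participants will be from that geographical area during the campaign period".
- **Balancing.** Data analysis: "Matching with replacement will be used to address potential imbalances between cohorts in baseline demographics". Under Participant-level data, the examples given of the cohorts' baseline demographic data are age, sex and education level. Sensitivity analyses are promised without content.
- **What else is collected.** Table 1 gives the time points for self-reported healthcare use as "Baseline, 3 months for each cohort". The cohort questionnaires include pain intensity and disability. Chronicity is also recorded, but is mentioned only for choosing interviewees.
- **Acknowledged limits.** The strengths and limitations list says "Cohort participants are anticipated to be primarily from the geographical region targeted by the media campaign, which may limit generalisability". The Discussion adds that causal inference is restricted without a randomised control.

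**The concern.** Three things change together between the cohorts: the version of the service, the region most callers come from, and the way callers are brought in. People who ring after local advertising may differ from people who found a national helpline unprompted. They may differ in how severe or long-standing the pain is, how much care they have already used, and what services are nearby. Each of these plausibly affects healthcare use, which is the outcome.

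Matching on age, sex and education would leave most of those differences in place. The protocol treats the regional concentration as a question of generalisability. It also bears on internal validity, because it applies to most of one cohort and presumably to very little of the other. If the plan is followed as written, a rate ratio below or above 1 may reflect who called and not what the upgraded service did.

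**Working it through.** **1. The plan's own numbers.** 208 / (1 − 0.15) = 244.7, rounded up to 245; 245 + 50 = 295. Both reproduce. The 208 cannot be checked directly because no dispersion is given.

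**2. Share of the post-upgrade cohort recruited after launch.** If the estimate of 50 pre-campaign participants holds, 245 − 50 = 195, and 195/245 = 0.796. This is an upper limit for the campaign-recruited share, since the helpline stays national and the protocol says most, not all. If just over half of the 195 are campaign-recruited (98), the share is 98/245 = 0.40.

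**3. Apparent rate ratio with no upgrade effect.** Let f be the campaign-recruited share and r the usage of those callers relative to other callers, whatever the service version. Apparent RR = (1 − f) + f·r. The values of r are assumptions; the documents give none.

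| r | f = 0.40 | f = 0.796 |
|---|---|---|
| 0.8 | 0.60 + 0.40 × 0.8 = 0.92 | 0.204 + 0.796 × 0.8 = 0.84 |
| 0.7 | 0.60 + 0.40 × 0.7 = 0.88 | 0.204 + 0.796 × 0.7 = 0.76 |
| 1.2 | 0.60 + 0.40 × 1.2 = 1.08 | 0.204 + 0.796 × 1.2 = 1.16 |

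The last row shows that the bias could equally hide a benefit. For scale, the design target is 6/10 = 0.60. Case mix alone would reach it at f = 0.796 only with r = (0.60 − 0.204)/0.796 ≈ 0.50.

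**4. Effect on the test.** Take the Wald variance of the log rate ratio, (1/μ₁ + k)/50 + (1/μ₂ + k)/208. Solve for the dispersion k that gives 80% power at RR 0.60, two-sided 5% (sidedness assumed). With 3-month means of 2.5 and 1.5, the required variance is (0.511/2.802)² = 0.0332, so k = (0.0332 − 0.0080 − 0.0032)/(1/50 + 1/208) ≈ 0.89. The standard error is about 0.18. At r = 0.8 the nominal 5% test then rejects about 7.5% of the time for f = 0.40 and about 16% for f = 0.796. Solving from 12-month means (10 and 6) gives k ≈ 1.23 and almost the same rejection rates.

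**5. Would matching on region solve it?** Hardly. The campaign region has 230 000 people. Assuming a national population of 25 to 28 million (not in the documents) and calls in proportion to population, 50 pre-upgrade participants would include 0.41 to 0.46 from that region. Even at five times that rate, only about two would. There is almost no overlap on region itself. Remoteness derived from postcode is a broader class and more usable.

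**6. The contrast that avoids the campaign.** With 50 pre-upgrade against the first 50 post-upgrade participants at RR 0.60, power is about 57% (k = 0.89, 3 months) to 59% (k = 1.23, 12 months). With 15% loss in both groups (42.5 each) it is about 51% to 52%.

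**The case against.** **The protocol does not say that demographics are all it will balance.** This stands as to wording. No further adjustment is excluded, sensitivity analyses are promised, and an analysis plan not shown here may name more variables. Under Secondary data, moreover, pain severity and area of residence are counted as demographic data, and Adoption counts rurality. A reader might infer that severity is ruled out of the model; the text does not support that. However, the Secondary data passage concerns a selection-bias check on routine helpline data, not this contrast, and prior healthcare use is not called a demographic anywhere. The protocol is not silent: it names a method and a target for it, and the target is too narrow.

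**A reader might infer that a baseline measure of prior use is in hand and ignored.** The documents do not establish this. Table 1 lists baseline as a time point but gives no recall window, the questionnaire falls up to 10 days after first use, and the instrument list is in an appendix not shown.

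**The region is described as similar to the country:** "The Mid North Coast region has a population of 230 000 broadly reflective of national demographics". That concerns demographics. It says nothing about severity, earlier care or local services, or about who responds to advertising.

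**The causal limitation is already acknowledged.** It is, in general terms. The change of region and recruitment route between cohorts is raised only as a limit on generalisability.

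**Conclusion.** The point holds in this form: the one balancing step the protocol names does not address the case-mix differences that its own recruitment plan makes likely, and better variables appear to be within reach. It should be dealt with before the analysis is fixed.

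The size and direction of any bias cannot be known from the documents. For callers who would use 20% fewer services anyway, the illustrative range is an apparent rate ratio of 0.92 to 0.84 with no upgrade effect, as their share of the post-upgrade cohort runs from 40% to 80%. It rests on an assumed usage difference, on about 50 participants being recruited before launch, and on how far most falls short of all. It does not show that the primary result will be wrong.

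Nor can a particular gain in power be claimed for adjustment. No dispersion is stated, and nothing in the documents says how much of the variation baseline use and severity would explain.

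**What to change.** **Extend the matching or adjustment set of the primary model.** Name baseline healthcare use, baseline pain intensity, disability, LBP chronicity and remoteness from postcode, in addition to age, sex and education. Confirm first that the baseline healthcare-use item refers to the period before the first call; if it does not, reword it or say that it cannot serve.

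**Split the post-upgrade cohort at campaign launch.** Report the rate ratio against the pre-upgrade cohort separately for those recruited before and after launch, with the pre-launch contrast labelled supportive only.

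**State the mechanism as a limitation.** Say that region and recruitment route change with the upgrade, and that this affects interpretation of the rate ratio as well as generalisability.

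**Cost.** Mostly analysis-plan wording, plus a check of one questionnaire item. There are two drawbacks. Baseline is completed up to 10 days after the call, so pain and disability scores may already be slightly affected by the service. The contrast with the first 50 has only about 50% to 60% power for a rate ratio of 0.60, and it reflects the service before it was refined for full implementation.
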